### Sample size calculation

The sample size calculation is based on the detection of significant differences in MAMA, one of the primary endpoint parameters of this trial. A clinical trial on enteral hyperalimentation in malnourished patients with cirrhosis and ascites [26] was used as an exemplary model. The rate was measured in percent per day, i.e. MAMA changes divided by number of days between admission and discharge. After eliminating the gross outlier of this study, the standard deviation of this rate was 0.21% per day. The clinically relevant difference was set to 0.1% MAMA per day. Therefore, the sample size necessary for the trial with a power of 80% and a two-sided significance level of 0.05 was calculated to be 71 patients per group. An assumed 10% drop-out rate in this trial (due to non-compliance, intolerance, premature discontinuation, etc) will raise the sample size to 78 patients per group. Therefore, at least a total of 156 patients have to be included to the trial in order to yield 142 completers.

### Randomization and treatment

Randomization (1:1) will be performed by the algorithm programmed in specific computer software and a randomization list will be prepared. The randomization list will be prepared by the institution that is responsible for the packaging of the study and control products and kept in safe and confidential custody at this institution. Both study product and control product will be of same form and appearance (powder) including the packaging material. If it is medically imperative to know which product the patient consumes, emergency envelopes contain the information on the subject's study product.

### Adverse events

All adverse events (AE) are recorded. Events related to the initial diagnosis for LT, to the transplantation procedure itself, or problems associated with routine procedures after transplantation, e.g., liver biopsy, are not to be noted as AE or serious adverse event (SAE) unless the investigator deems the events to be a cause of the study product. All SAE potentially associated with the application of study product must be documented on a SAE form which has to be sent to the principal investigator within 24 hours or latest on the following working day. The principal investigator ensures that SAE are reported to the safety board, ethics committee, and to further investigators, if applicable.

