### Objectives and endpoints

Primary objective is to determine the safety and efficacy of the long-term administration of immunonutrients, and assessment of the patients' nutritional and physiological status as well as quality of life, while waiting for a graft. Secondary Objective is to investigate the effects of immunonutrition on post-transplant morbidities.

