### Quality assurance

The study is performed according to the principles of the ICH-GCP consolidated guidelines as required by regulatory agencies [27] and the ethical principles according to the current revision of the Declaration of Helsinki [28] and local legal and regulatory requirements. The trial is monitored by HealthEcon AG according to standard operational procedures that is based on ICH-GCP guidelines.

An independent safety board monitors closely the proper conduct of the trial and all SAE reports to ensure the safety of the subjects during the course of the study.

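### Safety on the waiting list is a primary objective, but liver-disease events in that period enter the AE/SAE data only if the investigator attributes them to the product

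*Protocol article*

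**What the plan says.** Objectives and endpoints: "Primary objective is to determine the safety and efficacy of the long-term administration of immunonutrients", with the assessment placed in the period before a graft is available. Study nutrition stops on the day of transplantation (Subject recruitment), so the waiting-list period is the whole treatment period.

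The Adverse events section sets three rules in sequence:

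- General rule: "All adverse events (AE) are recorded".
- Exclusion: three classes, "Events related to the initial diagnosis for LT, to the transplantation procedure itself, or problems associated with routine procedures after transplantation", fall outside that rule. The section says that they "are not to be noted as AE or serious adverse event (SAE) unless the investigator deems the events to be a cause of" (here, the product), so attribution is the only way back in. Read literally the causal direction is reversed; an event caused by the product is evidently meant.
- SAE form: "All SAE potentially associated with the application of study product must be documented on a SAE form".

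Quality assurance then describes the board's role: "An independent safety board monitors closely the proper conduct of the trial and all SAE reports".

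**The concern.** The general rule and the exclusion cannot both be followed as written. The excluded classes include events of the disease for which every patient was listed. That disease is also the condition most easily confused with a product effect in this population. A blinded investigator looking at one patient with worsening liver disease has little basis for deciding whether the supplement contributed. A randomised trial answers that question by counting such events in each arm, whatever anyone thinks caused them. If the count depends on attribution, an excess in either arm could go largely unrecorded during the period in which the product is taken.

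The Discussion shows why this matters here. It says that a nutrient able to alter immune function needs critical evaluation for harm. Its reassurance in end-stage liver disease comes from a pilot in fifteen patients, reported as showing no consequences attributable to the product. That is attribution-based evidence, which a controlled comparison could improve on.

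**Working it through.** **Where a waiting-list liver event would be captured**

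1. *AE/SAE record.* Excluded unless the investigator attributes it to the product (Adverse events).
2. *SAE form.* The wording, potentially associated, is a lower threshold than attribution. But an excluded event is not an SAE at all until the investigator has attributed it, so for liver-disease events the stricter condition applies first.
3. *Safety board.* Its described safety input is the SAE reports, so it inherits the same filter.
4. *Listed outcomes* (Trial design and schedule). Ventilation, hospital stay, wound healing, infections, CRP, rejection and mortality are collected whatever the attribution, but as post-transplant investigations to week 12. Mortality is ICU, hospital, 28-day and week-12 survival. The pre-transplant list holds anthropometry, laboratory and endocrine values, energy expenditure, grip strength, respiratory function, fatigue and quality of life. It contains no clinical decompensation and no waiting-list death.
5. *Monthly laboratory values.* Albumin, bilirubin, INR, creatinine, urea and transaminases are measured in all patients. They give some view of liver and kidney function, but they are not clinical events and they stop when a patient dies or leaves the list.

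So a liver-related clinical event on the waiting list, including a fatal one, may appear in no listed safety comparison.

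**How much the filter could cost (illustration)**

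The plan gives no safety event rates and no safety power figure. Its only design figure is for mid-arm muscle area: 2 × (1.960 + 0.842)² × 0.21² / 0.1² = 69.2, or 70.2 with the t distribution, which rounds up to the stated 71 per group. Then 71 × 1.10 = 78.1 gives the stated 78. I use 78 per arm.

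Assumptions: true event rates p₁ and p₂, and a share q of events attributed to the product, equal in both arms because of blinding. Recorded rates are then qp₁ and qp₂. The ratio between arms is preserved and the difference shrinks by q.

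For a two-sided 5% test, with d the recorded difference and p̄ the mean recorded rate:

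- SE₀ = √[2p̄(1 − p̄)/78]
- SE₁ = √[(qp₁(1 − qp₁) + qp₂(1 − qp₂))/78]
- power = Φ[(d − 1.96 SE₀)/SE₁] + Φ[(−d − 1.96 SE₀)/SE₁]

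All events recorded, 0.40 v 0.60: SE₀ = 0.0801, SE₁ = 0.0784. (0.20 − 0.1569)/0.0784 = 0.55, so power is 0.71; the second term is negligible.

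Ten per cent attributed, 0.04 v 0.06: SE₀ = SE₁ = 0.0349. (0.02 − 0.0684)/0.0349 = −1.39 gives 0.083, and (−0.02 − 0.0684)/0.0349 = −2.54 gives 0.006. The sum is 0.09.

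The same formula over a range of assumed rates:

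| Share attributed | 40% v 60% | 30% v 50% | 20% v 40% |
|---|---|---|---|
| 100% | 71% | 73% | 78% |
| 50% | 30% | 34% | 42% |
| 20% | 13% | 15% | 18% |
| 10% | 9% | 10% | 11% |
| 5% | 7% | 7% | 8% |

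For 40% v 60%, a 10% share leaves 78 × 0.04 = 3.1 v 78 × 0.06 = 4.7 expected events, so the normal approximation is rough in the lower rows. The direction is not in doubt.

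**The case against.** The strongest reply is that much harm data survive. Post-transplant infections, rejection, ventilation and death are collected in every patient regardless of attribution. AEs outside the excluded classes are recorded in both arms, with weekly calls that ask about them. Monthly laboratory values would show some differences in liver or kidney function, and the Statistics and data management section counts them against normal ranges. All of this stands. A reader might infer from the exclusion that the arms cannot be compared for harm at all, or that the safety objective is unanswerable; the document does not support that.

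A reader might also infer that the filter favours one arm. In a double-blind trial attribution should be roughly equal between arms, so the expected effect is lost events and lost power.

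The power figures can fairly be called true by construction: discarding most events lowers power, and no rate or share comes from the document. They show scale and are not an estimate. At a 50% share the loss is smaller, though still large.

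Finally, the article condenses a fuller protocol, and the reason a patient left the list would presumably be known from follow-up. But the exclusion is stated outright here, so this is not a case of detail left to another document. Knowing that a patient died is also not the same as planning to count such deaths by arm.

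**Conclusion.** The point holds for one class of events in one period: clinical liver-disease events, including deaths, between randomisation and transplantation. As written, these cannot be compared between arms from the AE/SAE data, and the board as described would not see those left unattributed. This is the treatment period to which the primary safety objective refers, and no other listed outcome fills the gap.

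The size depends on the true event rates and on how often blinded investigators attribute events to the product, neither of which the document gives. Under the assumed rates in the table, power falls from 71–78% with full recording to 9–11% at a 10% share and 30–42% at a 50% share. The conclusion that a comparison is lost rests on the text alone and needs none of these assumptions. Events not recorded at the time may not be fully recoverable later, so the rule should be changed before enrolment starts.

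**What to change.** In the Adverse events section, remove attribution as a condition for recording, so that the section agrees with its own general rule. Record all AEs and SAEs from randomisation to transplantation in both arms, including liver-disease events and waiting-list deaths, and enter the investigator's view of relatedness as a separate field. State that these events will be compared by arm and that the safety board receives all SAEs, whether or not they are attributed to the product. Expected events of the underlying disease may be exempt from expedited reporting but not from recording. Post-transplant events already collected as outcomes need not be entered a second time. Correct the reversed causal wording in the same edit.

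The cost is additional eCRF entries drawn from the weekly calls and monthly visits that already take place. No visit or test is added.

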### Quality assurance

The study is performed according to the principles of the ICH-GCP consolidated guidelines as required by regulatory agencies [27] and the ethical principles according to the current revision of the Declaration of Helsinki [28] and local legal and regulatory requirements. The trial is monitored by HealthEcon AG according to standard operational procedures that is based on ICH-GCP guidelines.

An independent safety board monitors closely the proper conduct of the trial and all SAE reports to ensure the safety of the subjects during the course of the study.

### Statistics and data management

All analyses will be carried out on an "intent-to-treat" basis. However, attempts will be made to analyze "per protocol", "completer", and "intent-to-treat" populations separately, when statistically appropriate. Repeated-measures analysis of variance (ANOVA) will be used followed by t-test when significant differences are detected by ANOVA. Pearson Chi-square test or Fisher's exact test will be used when appropriate. Times to an event are described by Kaplan-Meier and compared between groups by the log-rank test. The differences of the analysis variables are tested with the paired t-test or, in case of uneven distribution, the Wilcoxon-test (2-sided) for within group comparison. The Mann-Whitney U test will be used to detect differences between study groups. The following statistical values will be calculated where appropriate: mean, standard deviation, 95%-confidence interval of the mean, minimum, lower quartile, median, upper quartile, maximum, valid number, frequency count, and percentage. The laboratory values will be counted according to their normal ranges (below normal, normal, and above normal). Biometric analysis will be defined in the statistical analysis plan which has to be authorized before unblinding by the biometrician, the sponsor, and the principal investigator. One interim analysis will be performed after half of the patients have finished the clinical period for the primary endpoints.

All patient data (clinical and resource use) generated during the study will be recorded on the eCRFs specifically designed to meet the data recording requirements of the clinical study protocol provided by HealthEcon AG. All data management activities will be done according to ICH-GCP guidelines. Responsibility for data management is with HealthEcon AG, Basel, Switzerland. Throughout the study, all patient information in the eCRF will only be identifiable by means of an identification number (patient number) and possibly patient initials.

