### Trial design and schedule (Fig. 1)

**Figure 1 F1:**
[figure not shown]
**Scheme depicting the workflow of the study**. Each subject will be recruited on the day of registration on the waiting list for liver transplantation after giving informed consent. Study nutrition ends on the day of transplantation. Subjects are randomized to two parallel groups treated for study or control product. Furthermore, patients will be followed for 12 weeks after transplantation.

Site number, patients' randomization number and initials, all demographic data (date of birth, sex, height, weight), medical history (including a complete dietary history and MELD score), physical examination, comorbidities, and concomitant medications are documented on day one. Furthermore, anthropometric, physiologic, and biochemical measurements are carried out and documented. The aforementioned measurements are performed during monthly visits until transplantation. The patients consume either the study product (ORAL IMPACT^®^) (Table 2) or control product (IMPACT-control supplement) (Table 2) once a day for the period of waiting until a graft is available. During each visit, the following data are recorded in the electronic case report form (eCRF):

**Table 2 T2:** Composition of ORAL IMPACT^® †^and IMPACT Control supplement (in powder form)

Content (1 Sachet)		**ORAL IMPACT^® ^**(74 g)	**IMPACT Control **(74 g)
-Protein	g	16.7	13.0
-Casein/Whey	g	(13)	(13)
-L Arginine	g	(3.74)	-
-Fat	g	8.3	8.3
-Essential FA (LA+LNA)	g	(0.94)	(2.6)
-n-6-FA (LA)	g	(0.74)	(2.6)
-n-3FA (EPA+DHA+LNA)	g	(1)	-
Carbohydrates	g	40.2	43.94
Fibres	g	3	3
RNA	mg	390	-
Energy	g	302.8	302.8
-kcal/ml		§	§
-P:F:C	%	22:25:53	17:25:58
Sodium	mg	320	320
Potassium	mg	402	402
Calcium	mg	240	240
Magnesium	mg	80	80
Phosphorus	mg	216	216
Chloride	mg	480	480
Iron	mg	3.6	3.6
Copper	mg	0.5	0.5
Manganese	mg	0.6	0.6
Zinc	mg	4.5	4.5
Fluoride	mg	0.5	0.5
Iodine	mcg	45	45
Chromium	mcg	30	30
Molybdenum	mcg	60	60
Selenium	mcg	14	14
Retinol (Vit. A.)	mg	0.3	0.3
Calciferol (Vit. D)	mcg	2	2
Tocopherol (Vit. E)	mg	4	4
Phyllochin. (Vit. K1)	mg	20	20
Thiamine (Vit. B1)	mg	0.36	0.36
Riboflavine (Vit. B2)	mg	0.52	0.52
Pyridoxine (Vit. B6)	mg	0.44	0.44
Cyanocobal. (Vit. B12)	mcg	1.2	1.2
Ascorbic Acid (Vit. C)	mg	20	20
Biotin	mcg	30	30
Folic Acid	mcg	60	60
Niacinamide	mg	4.8	4.8
Pantothenic Acid	mg	2.4	2.4

^†^; IMPACT^® ^is a food for special medical purpose (FSMP)

§ content of sachet to be dissolved in 250 ml water for each serving

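### The named between-group tests are all unadjusted and day-one MELD has no stated role, which forgoes modest precision on the post-transplant outcomes

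*Protocol article*

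**What the plan says.** All references are to the protocol article.

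- **Statistics and data management** lists the methods generically. For categorical data, "Pearson Chi-square test or Fisher's exact test will be used when appropriate". For survival-type data, "Times to an event are described by Kaplan-Meier and compared between groups by the log-rank test". For other variables, "The Mann-Whitney U test will be used to detect differences between study groups". For repeated measurements, "Repeated-measures analysis of variance (ANOVA) will be used followed by t-test when significant differences are detected by ANOVA". None is described as adjusted or stratified, and no regression model appears anywhere in the article.
- The same section leaves the detail open: "Biometric analysis will be defined in the statistical analysis plan which has to be authorized before unblinding".
- **Trial design and schedule (Fig. 1)** has severity recorded at entry: "medical history (including a complete dietary history and MELD score), physical examination, comorbidities, and concomitant medications are documented on day one". MELD is not mentioned again outside the abbreviation list.
- **Randomization and treatment** gives a 1:1 ratio and names no stratification factor.
- **Objectives and endpoints** sets the status of the outcomes concerned: "Secondary Objective is to investigate the effects of immunonutrition on post-transplant morbidities". These outcomes (ventilation, stay, wound healing, infections, rejection, mortality) are followed for 12 weeks after transplantation.

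**The concern.** Mid-arm muscle area, grip strength and quality of life each have a day-one value against which change can be measured. Ventilation time, hospital stay, infection, rejection and death do not. For these, the natural way to use baseline information is a severity measure taken at listing, and one is already collected.

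The article itself makes severity plausible as a predictor, though only indirectly. The Discussion says that the prevalence of malnutrition depends partly on how severe the liver insufficiency is. The Background links malnutrition to longer stay, longer ventilation, more morbidity and higher mortality.

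Two things are at stake. One is precision: the trial is sized on muscle area alone, and no power is stated for any post-transplant outcome. The other is balance. The patients compared are those who received a graft, a subset formed after randomisation and after a wait on the assigned product. Randomisation does not guarantee equal severity in that subset, and the tests as described do nothing about a difference.

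**Working it through.** **Inputs from the document (Sample size calculation).** Difference 0.1% per day, SD 0.21% per day, two-sided 0.05, power 80%, 71 per group.

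**The plan's own figure.** n = 2 × (1.96 + 0.84)² × (0.21/0.1)² gives 70 after rounding up. The t-test version gives 70.2, so 71. The stated 71 reproduces, and power at 71 is 0.81. The figure concerns muscle area; below, 71 per arm serves only as a working size for the post-transplant comparison.

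**Inputs not in the document.** Event rates after transplantation, the strength of the MELD-outcome association and the number transplanted per arm are all assumed.

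**Continuous outcome.** Take a standardised difference of 0.1/0.21 = 0.476, as in the plan. Adjusting for a covariate with correlation r multiplies the residual SD by √(1 − r²). Power = Φ[0.476 / (√(1 − r²) × √(2/71)) − 1.96]. The last column is 71 × [1/(1 − r²) − 1], the extra patients per arm that an unadjusted analysis needs for the same precision.

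| r | Power | 1/(1 − r²) | Extra per arm |
|---|---|---|---|
| 0 | 0.81 | 1.00 | 0 |
| 0.2 | 0.83 | 1.04 | 3 |
| 0.3 | 0.84 | 1.10 | 7 |
| 0.4 | 0.87 | 1.19 | 14 |
| 0.5 | 0.91 | 1.33 | 24 |

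**Binary outcome.** Simulation of 3,000 trials per setting, 71 per arm, marginal rates 40% and 20%. An unadjusted chi-square test is compared with a likelihood-ratio test from logistic regression on treatment and MELD.

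| Odds ratio per SD of MELD | Unadjusted | Adjusted |
|---|---|---|
| 1.0 | 0.767 | 0.769 |
| 1.5 | 0.751 | 0.762 |
| 2.0 | 0.756 | 0.776 |
| 3.0 | 0.751 | 0.826 |

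The Monte Carlo standard error of one entry is √(0.75 × 0.25/3000) = 0.008. A second scenario (50% event rate for a control patient of average MELD, conditional treatment odds ratio 0.39, 1,500 trials) gave 0.736 against 0.765 at an odds ratio of 1.65 per SD, and 0.670 against 0.737 at 2.46. The gain therefore depends on the assumed event rate and effect as well as on MELD.

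**Imbalance.** By chance alone, the difference in mean MELD between arms of 71 has standard error √(2/71) = 0.168 SD, so 95% of differences lie within ±1.96 × 0.168 = ±0.33 SD. The nominal error rate already covers this. A systematic shift among transplanted patients is not covered. The table gives the type I error of the unadjusted test with 40% events in both arms.

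| Odds ratio per SD | No shift | 0.2 SD shift | 0.3 SD shift |
|---|---|---|---|
| 1.5 | 0.049 | 0.056 | 0.064 |
| 2.0 | 0.051 | 0.069 | 0.089 |
| 3.0 | 0.048 | 0.084 | 0.124 |

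The adjusted test stays between 0.050 and 0.058 throughout, but the simulation puts the whole imbalance into day-one MELD, which is the best case for adjustment.

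**The case against.** The strongest reply is that covariates for secondary outcomes are ordinary SAP content, that the article is condensed, and that it expressly leaves the biometric analysis to an SAP authorised before unblinding. This stands to a large extent. A reader might infer that the listed tests are the only ones planned and that MELD has been ruled out; the document says neither. The tests are listed generically, none is tied to the post-transplant outcomes, and the log-rank test and two-by-two tables can both be stratified by MELD without contradicting the text. What remains is that the article does commit to named tests, all described without adjustment, so it is better to settle the point than leave it to inference.

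A reader might also infer that unadjusted tests are invalid. They are not: under randomisation they hold their error rate, as the no-shift column shows. The inflated rates need a systematic severity difference between the transplanted groups, and nothing in the document shows that one will arise.

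The prognostic strength of MELD is likewise assumed. At r = 0.1, power is still 0.81, and the binary gain is slight unless the association is strong.

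Nor is 71 per arm a ceiling. The Sample size calculation section includes 78 per group to yield 71 completers, and the main analysis is by intention to treat. Equally, fewer may reach a graft.

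Finally, adjustment does not remove selection into transplantation. Severity can change over a wait of several months, and the product may affect who is transplanted.

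**Conclusion.** The point holds as a suggestion for improvement. Every between-group test named is unadjusted, and day-one MELD is collected without a stated use in analysis or randomisation. The cost is some lost precision, and no correction of differences in listing severity, on outcomes that belong to the secondary objective.

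With 71 per arm and the 40% against 20% scenario, the power forgone is about 0 to 2 points for odds ratios up to 2 per SD of MELD, and 7 to 8 points at 3. For a continuous outcome at the plan's standardised difference, it is about 2 to 10 points for r between 0.2 and 0.5 (0.81 against 0.83 to 0.91). All of this rests on associations that the document does not give. The protection against selection-related imbalance is partial at best. The primary analysis is not affected, and the stated analysis of the secondary outcomes is not invalid.

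**What to change.** Before unblinding, state in the SAP, and align the protocol wording, that the between-arm estimate for post-transplant outcomes is adjusted for MELD as recorded on day one. Later values follow the start of the product and should not replace it. Use logistic regression for infections and rejection, and a Cox model or MELD-stratified log-rank test for times to an event. Keep the named unadjusted tests and report them alongside.

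The cost is a few lines of wording and code, since the covariate is already recorded. The limits to state with it are:

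- Adjusted odds and hazard ratios are conditional effects and will differ numerically from the unadjusted ones.
- With few deaths, the mortality analysis may support only the unadjusted comparison or a model with MELD as its single covariate.
- Hospital stay and ventilation time need a stated handling of patients who die early before any adjusted model is fitted.
- Day-one MELD corrects only part of any selection into transplantation, so the number transplanted and their day-one MELD should be reported by arm.
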